### Follow up assessments

Outcomes are measured at six months to determine short–term changes to the end of the intervention and 1 year to determine whether change is sustained.

### Statistical justification for sample size

The sample size has been determined to detect a significant difference in the SGRQ at 1 year. To have 80% power to detect a difference of 4 points (which is the minimal clinically significant difference [26] from a baseline total value of 39 [50], with a standard deviation of 15) at the 5% level of significance, 445 evaluable participants are required. We aim to recruit 556 participants, which allows for a 20% loss to follow-up.

This sample size is more than sufficient to detect an increase in physical activity in the intervention group. Assuming the intervention arm reaches 89 minutes of moderate intensity physical activity/week, and the control arm 55 minutes (SD = 70 mins), for 90% power at a 5% significance level, a sample size of 90 patients in each arm is required (in absence of good COPD data, EXERT trial data used) [55]. Accounting for 20% loss-to follow-up, we therefore require a total of 225 patients. To estimate the power for smoking cessation we have taken a smoking prevalence of 45% [56]. Estimates of the likely quit rate are 34% in the intervention arm and 9% in the usual care arm (estimates from Cochrane review of nurse-led interventions for smoking cessation [53]). Our proposed sample size of 278 per group is sufficient to achieve power of 75%, at the 5% significance level.

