#### Smoking cessation

The nurse provides information about the health consequences of smoking and sends a booklet with details about the benefits of smoking cessation. The pros and cons for the individual of smoking cessation are discussed. Participants are encouraged to commit to approaching the smoking cessation service and to set a goal to read the smoking cessation literature or contact the service. Any goals are reviewed at subsequent telephone consultations and discrepancy between goals and actions discussed. Participants willing to consider smoking cessation are encouraged to seek social support from family and friends in their quit attempt. Written prompts also provide information about local smoking cessation services in case of relapse or for those not ready to change early on in the intervention period.

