### Analysis

All data will be analysed by intention to treat. A comparison between groups for the primary outcome measures (health related quality of life) will be made at 1 year to assess the long-term effect of the self-management intervention.

For outcomes measured on a continuous scale (HRQoL, physical activity, EuroQol EQ-5D), analysis of covariance will be used; i.e. a linear regression where the final score is regressed against treatment group and adjusted for baseline score. Model assumptions will be checked and a transformation for Normality used if necessary. Binary outcomes will be analysed using logistic regression and recurrent outcomes (e.g. number of hospital admissions) will be analysed using Poisson regression with an offset term for the length of follow-up. Differences between treatment groups will be summarised with suitable effect estimates (e.g. mean difference, relative rate) with 95% confidence intervals. A 5% statistical significance level will be used. Levels and patterns of missing data will be assessed and summarised, and if appropriate, suitable methods (e.g. regression imputation using baseline data) will be used to evaluate any effect this might have on the conclusions.

We will undertake exploratory subgroup analyses to explore the effects of the intervention in a subgroup who actively engage with the intervention (through increased physical activity, uptake of smoking cessation support or checking of inhaler technique) and those who increase their self-efficacy for COPD self-management. Additionally we will explore effectiveness in subgroups by baseline level of self-efficacy, depression and anxiety scores and HRQoL and participant characteristics (age, sex, ethnicity and number of co-morbidities).

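### The 75% power quoted for smoking cessation is not the power of the quit-rate comparison described, which is about 99%; it fits only an unnamed endpoint with no loss to follow-up

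*Protocol article*

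**What the plan says.** The section on sample size in the protocol article contains three calculations. The first, for the SGRQ, sets the trial's size: 445 evaluable participants, and then "We aim to recruit 556 participants, which allows for a 20% loss to follow-up". The second, for physical activity, needs 90 per arm and is inflated for the same 20% loss to 225 in total.

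The third concerns smoking. The inputs are "To estimate the power for smoking cessation we have taken a smoking prevalence of 45" per cent, and "Estimates of the likely quit rate are 34% in the intervention arm and 9% in the usual care arm". The conclusion is "Our proposed sample size of 278 per group is sufficient to achieve power of 75%, at the 5% significance level". The article does not give the denominator (baseline smokers or all participants), the test, or whether loss to follow-up was allowed for.

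The Outcomes section lists smoking as a self-reported health behaviour among the secondary outcomes. The Analysis section assigns logistic regression to binary outcomes, reports effect estimates "with 95% confidence intervals" and says "A 5% statistical significance level will be used".

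**The concern.** The sentence presents itself as the power for cessation and takes quit rates as its effect size. A quit rate is a proportion of smokers, and the 45% is what turns 278 participants per arm into a number of smokers. A contrast of 34% with 9% in 100 or more smokers per arm is very large, and 75% looks far too low for it.

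Smoking is one of the trial's additional aims and a component of the intervention, so the figure will be used to say what the trial could have shown on it. As printed, it is either more than 20 percentage points too low (if cessation is meant) or about 5 to 11 points too high for the sample expected at follow-up (if smoking prevalence is meant). The reader cannot tell which.

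**Working it through.** **Inputs, all from the sample size section of the article unless noted**
- 278 per arm recruited. With 20% loss, 556 × 0.8 = 444.8, or about 222 per arm.
- 45% smokers: 278 × 0.45 = 125.1 per arm; after loss, 125.1 × 0.8 = 100.1 per arm.
- Quit rates 34% and 9%.
- 5% level. Two-sided is an assumption, consistent with the 95% intervals in the Analysis section.

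**The neighbouring calculations reproduce**
- SGRQ: 2 × (1.960 + 0.842)² × 15² / 4² = 220.7, so 221 per arm, against 445 in total in the article. 445 / 0.8 = 556.25, against 556.
- Physical activity: 2 × (1.960 + 1.282)² × 70² / 34² = 89.1, so 90 per arm. 180 / 0.8 = 225, as stated.

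**Formula for two proportions**, pooled variance under the null:

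power = Φ{ [ |p1 − p2| − 1.960 × √(2p̄(1 − p̄)/n) ] / √( [p1(1 − p1) + p2(1 − p2)]/n ) }, where p̄ is the mean of p1 and p2. The continuity-corrected version subtracts 1/n from |p1 − p2|.

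**Reading A: quitting among baseline smokers, 34% v 9%** (p̄ = 0.215)
- n = 100: (0.25 − 1.960 × 0.0581) / 0.0553 = 2.46, power 99.3%. Continuity-corrected 98.9%, Fisher exact 99.1%.
- n = 125: (0.25 − 1.960 × 0.0520) / 0.0495 = 2.99, power 99.9%. Both the corrected and the Fisher figures are 99.8%.
- 75% power would need only about 37 smokers per arm (45 with continuity correction).

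**Reading A2: quitters over everyone randomised**
- 0.45 × 0.34 = 15.3% v 0.45 × 0.09 = 4.05%.
- n = 278: 99.5%. n = 222: 98.2%.

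**Reading B: still smoking, among everyone randomised**
- 0.45 × (1 − 0.34) = 29.7% v 0.45 × (1 − 0.09) = 40.95%; rounded, 30% v 41%.
- Example, n = 278, unrounded, corrected: (0.1125 − 0.0036 − 1.960 × 0.0405) / 0.0403 = 0.73, power 76.8%.

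| Per arm | Rates | Uncorrected | Continuity-corrected | Fisher exact |
|---|---|---|---|---|
| 278 (no loss) | 29.7% v 40.95% | 79.4% | 76.8% | 76.9% |
| 278 (no loss) | 30% v 41% | 77.5% | 74.7% | 74.8% |
| 222 (20% loss) | 29.7% v 40.95% | 70.0% | 66.4% | 66.9% |
| 222 (20% loss) | 30% v 41% | 67.9% | 64.2% | not computed |

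Neither cessation reading comes near 75%. Reading B does so with a corrected or exact test at 278 per arm, most closely with rounded rates. With 20% loss it falls to 64% to 70%.

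**The case against.** The best defence is that the 75% is a sound calculation for an endpoint the article describes incompletely. Reading B uses exactly the four printed inputs. The power is attached to the whole 278 per group, not to a subset of smokers; the listed outcome is smoking, not quitting among baseline smokers; and analysis is by intention to treat. This stands to the extent that a reader should not infer that 75% is unobtainable from the stated inputs. It can be obtained, and it may well have been obtained in this way.

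It does not rescue the sentence. Reading B is an inference: the text speaks of smoking cessation and quit rates, and names neither prevalence in all participants nor a corrected or exact test. It may be said that the article openly ties 75% to the recruited number and does not promise it after loss. That is so, but the same section inflates its other two calculations for 20% loss and gives no reason for treating this one differently.

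A condensed article may leave analysis detail to a fuller document. The point here is not an omission, however: a definite figure is printed beside a comparison that it does not match.

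It is also fair that the consequence is limited. On the cessation reading the error is conservative, and a null result would be read mainly from its confidence interval.

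**Conclusion.** The point holds in a limited form. For the comparison named, power is about 99%, not 75%. The 75% is recovered for smoking prevalence among all randomised, with a corrected or exact test and complete follow-up; with the 20% loss used elsewhere in the section, that becomes about 64% to 70%. These figures assume a two-sided 5% test, equal allocation and, where loss is applied, the same loss among smokers and non-smokers. They come from unadjusted two-proportion tests, not from the planned logistic regression.

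Two stronger readings should be resisted. One is that the trial is the wrong size: the sample size rests on the SGRQ, and that calculation and the physical activity one both reproduce. The other is that 34% is too optimistic because the nurse merely refers smokers on, so that the trial is weak for any realistic effect. The article does say "Participants are encouraged to commit to approaching the smoking cessation service", but the same section also describes health information, discussion of pros and cons, goal setting with review at later calls, encouragement of social support and written materials. Whether 34% transfers depends on a cited review that is not at hand, and the documents give no smaller effect to test against.

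This is a moderate correction to one statement about a secondary outcome.

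**What to change.** Rewrite the smoking part of the sample size section to name the endpoint, the denominator, the test and the evaluable number per arm, and give the power for that combination:

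- If the analysis is quitting among baseline smokers: 34% v 9%, about 100 evaluable smokers per arm after 20% loss, power about 99%.
- If the analysis is smoking prevalence at follow-up in all participants: about 30% v 41%, 222 evaluable per arm after 20% loss, power about 64% to 70% depending on the test and on rounding of the rates. Give the single value for the test chosen.

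The investigators must say which was intended, since the article does not settle it. If 75% is kept for the second option, state that it assumes no loss to follow-up and a corrected or exact test. The cost is one paragraph; sample size and trial conduct do not change.

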### Analysis

All data will be analysed by intention to treat. A comparison between groups for the primary outcome measures (health related quality of life) will be made at 1 year to assess the long-term effect of the self-management intervention.

For outcomes measured on a continuous scale (HRQoL, physical activity, EuroQol EQ-5D), analysis of covariance will be used; i.e. a linear regression where the final score is regressed against treatment group and adjusted for baseline score. Model assumptions will be checked and a transformation for Normality used if necessary. Binary outcomes will be analysed using logistic regression and recurrent outcomes (e.g. number of hospital admissions) will be analysed using Poisson regression with an offset term for the length of follow-up. Differences between treatment groups will be summarised with suitable effect estimates (e.g. mean difference, relative rate) with 95% confidence intervals. A 5% statistical significance level will be used. Levels and patterns of missing data will be assessed and summarised, and if appropriate, suitable methods (e.g. regression imputation using baseline data) will be used to evaluate any effect this might have on the conclusions.

We will undertake exploratory subgroup analyses to explore the effects of the intervention in a subgroup who actively engage with the intervention (through increased physical activity, uptake of smoking cessation support or checking of inhaler technique) and those who increase their self-efficacy for COPD self-management. Additionally we will explore effectiveness in subgroups by baseline level of self-efficacy, depression and anxiety scores and HRQoL and participant characteristics (age, sex, ethnicity and number of co-morbidities).

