### Intervention

The intervention comprises a self-management package of four components: smoking cessation advice; encouragement to become physically active; correct inhaler technique and medication adherence. For those participants with recurrent exacerbations who have an action plan and rescue pack of antibiotics or steroids, there is an exploration of their confidence in identifying an exacerbation early and commencement of medication.

In keeping with best practice the intervention includes education, monitoring and assessment of progress and teaches skills with the aim of increasing self-efficacy [41-43]. We have also taken into account the best evidence for the promotion of physical activity [38,44,45].

The intervention is delivered by telephone by a nurse with one initial 35–60 minute coaching session one week post randomisation followed by three 15–20 minute telephone contacts over a three month period (at approximately weeks 3, 7 and 11) with individually tailored written supportive materials following telephone contacts (e.g. summary of goals agreed, physical activity diary, contact details for local services, information leaflet showing correct inhaler technique). This is followed by standard written prompts/information at 16 and 24 weeks. The first consultation addresses all the elements of the intervention, with subsequent ones addressing physical activity and other elements as appropriate. The intervention components are summarised in Table 1.

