### Intervention fidelity

A sample of telephone consultations are being recorded with the participants consent. These will be assessed according to delivery of the planned components, the use of behavioural change techniques and patient centred approach. The nurses delivering the intervention record the number of contacts and actions taken; these records will be used to assess the proportion of the intervention participants who participated in the intervention, the number of calls per participant and the number who completed all six intervention contacts.

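### The stated primary model ignores which nurse coached whom; if nurses differ in effectiveness and the result is meant to apply beyond them, its confidence interval is too narrow

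*Protocol article*

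**What the plan says.** - **Delivery.** The Intervention section states: "The intervention is delivered by telephone by a nurse with one initial" coaching session, with three shorter calls to follow. Intervention fidelity shows that more than one nurse is involved: "The nurses delivering the intervention record the number of contacts and actions taken". The article does not say how many.
- **Comparator.** Under Usual care, the control group gets a printed leaflet and no coach.
- **Allocation.** Individuals are randomised, stratified by four centres.
- **Primary model.** ANCOVA, spelled out in the Analysis section as "a linear regression where the final score is regressed against treatment group and adjusted for baseline score". It has no nurse term and no allowance for clustering.
- **Sample size.** "To have 80% power to detect a difference of 4 points", "with a standard deviation of 15) at the 5% level of significance, 445 evaluable participants are required". Then: "We aim to recruit 556 participants, which allows for a 20% loss to follow-up". No design effect is mentioned.
- **Reach of the conclusion.** The Discussion presents the service as a possible template for wider delivery and expects the trial to inform practice across the UK.

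**The concern.** The treatment is a series of conversations about goals, barriers and confidence, so its effect may depend on who conducts them. Participants coached by the same nurse would share that nurse's effect, while usual-care participants share nothing comparable. This is a partially nested design, with clusters in one arm only. Individual randomisation within centres does not balance the nurse effect out, because it arises after randomisation and only in one arm.

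Any positive between-nurse variance adds to the variance of the intervention-arm mean, and a regression with independent errors leaves that out. What is at stake is the precision claimed for the 4-point SGRQ comparison. A positive result could also be read as showing that coaching works in general when much of it came from particular coaches.

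**Working it through.** **Inputs from the protocol article:** difference 4 points, SD 15, 5% significance level (taken as two-sided), 80% power, 445 evaluable, 556 recruited, 20% loss, equal arms (278 per group).

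**Assumed, because the article does not give them:** number of nurses K, ICC, equal caseloads, large-sample normal approximation.

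**1. Reproduce the plan's figure.** n per arm = 2 × (1.960 + 0.842)² × 15² / 4² = 220.8, so 221 per arm and 442 in total. The t-test version gives 222 per arm, 444 in total. Both agree with 445, and 445 / 0.8 = 556.25 agrees with 556. The calculation therefore assumes full independence.

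**2. Standard error under independence.** With 445 / 2 = 222.5 per arm, SE = 15 × √(2 / 222.5) = 1.422.

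**3. Standard error with nurses nested in one arm.** Caseload m = 222.5 / K; design effect DE = 1 + (m − 1) × ICC; SE = 15 × √((1 + DE) / 222.5).

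Example, K = 4 and ICC 0.01: m = 55.6, DE = 1.55, SE = 1.605, ratio 1.605 / 1.422 = 1.13.

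**4. Consequences.** The type I error of the planned test is 2 × (1 − Φ(1.96 / ratio)), and coverage is its complement. Power of a test that uses the correct SE is Φ(4 / SE − 1.96).

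| K | ICC | DE | SE ratio | Coverage of nominal 95% CI | Type I error, planned test | Power, test with correct SE |
|---|---|---|---|---|---|---|
| 4 | 0.01 | 1.55 | 1.13 | 91.8% | 8.2% | 70% |
| 4 | 0.02 | 2.09 | 1.24 | 88.5% | 11.5% | 62% |
| 4 | 0.05 | 3.73 | 1.54 | 79.7% | 20.3% | 45% |
| 10 | 0.01 | 1.21 | 1.05 | 93.8% | 6.2% | 76% |
| 10 | 0.05 | 2.06 | 1.24 | 88.7% | 11.3% | 62% |
| 20 | 0.01 | 1.10 | 1.03 | 94.4% | 5.6% | 78% |
| 20 | 0.05 | 1.51 | 1.12 | 92.0% | 8.0% | 71% |

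With ICC 0 the ratio is 1 and nothing changes.

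**5. Power of the test as planned.** The uncorrected test rejects when the estimate exceeds 1.96 × 1.422 = 2.787, so its power is Φ((4 − 2.787) / SE). With 4 nurses:

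- ICC 0.01: Φ(1.213 / 1.605) = 77%
- ICC 0.02: Φ(1.213 / 1.768) = 75%
- ICC 0.05: Φ(1.213 / 2.187) = 71%

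These are the figures for the analysis as stated. The last column of the table belongs to a corrected test. All the power figures use the SD before baseline adjustment.

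**6. What the ICCs mean in SGRQ points.** Between-nurse SD = 15 × √ICC: 1.5 points at 0.01, 2.1 at 0.02 and 3.4 at 0.05.

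**The case against.** **The size is unknown.** This stands. The article gives neither K nor an ICC. A reader might infer that a handful of nurses deliver the coaching, but the text supports only the plural. A reader might also take the fidelity checks as evidence that delivery is expected to vary; checking fidelity does not show that. With 10 or 20 nurses and ICC 0.01 the effect is close to negligible.

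**The top of the range is extreme.** This also stands. ICC 0.05 implies a between-nurse SD of 3.4 points against a 4-point target. If nurse effects are normal around a mean benefit of 4, Φ(−4 / 3.35), or about 12% of nurses, would make patients worse. Contact is four calls ending around week 11, and the outcome is at 12 months.

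**The inflated type I error needs a particular null.** If coaching does nothing for anyone, treatment-induced nurse variance is zero and the error stays at 5%. Inflation requires nurse effects that differ but average zero, and inference to nurses beyond those employed. For the effect as delivered by these nurses, the ANCOVA interval is not too narrow on this account. That narrower target is defensible for a pragmatic trial, but it fits poorly with a Discussion that offers the service as a template.

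**The analysis plan may deal with it.** It may, and a supplementary analysis absent from a condensed article would not by itself be a finding. Here, though, the article does not leave the model open: it states one, and that model omits the nurse.

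**Baseline adjustment helps.** It raises power by an amount the article does not give. It does not repair the interval, because baseline SGRQ precedes coaching and cannot explain differences that coaching creates.

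**Conclusion.** The point holds conditionally. The stated interval is too narrow if nurses differ in effectiveness and the conclusion is meant to extend beyond the nurses employed. If either condition fails, it is not.

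Under assumed ICC 0.01, the understatement of the SE is about 13% with 4 nurses, 5% with 10 and 3% with 20. ICC 0.05 with 4 nurses (54%) should be read as an upper bound, not an expectation.

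Two stronger readings go beyond the documents. One is that the SE is understated and false positives exceed 5% as a matter of fact; without K or an ICC this cannot be asserted. The other is that the trial's power is really 45% and not 80%. That figure belongs to a corrected test at the upper bound; the planned test would have about 71% under the same assumptions.

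This is an inexpensive improvement to a stated model, not a flaw that invalidates the primary analysis.

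**What to change.** 1. Keep the coaching nurse's identifier in the contact records the nurses already complete, linked to each participant.
2. Leave the ANCOVA as the primary analysis.
3. Pre-specify a sensitivity analysis of 12-month SGRQ with a partially nested mixed model: baseline score and arm, a nurse random effect in the intervention arm only, arm-specific residual variances and a small-sample degrees-of-freedom correction.
4. If there are too few nurses to estimate the variance, show the interval over a stated ICC range instead, for example 0 to 0.05.
5. Report the number of nurses and the estimated ICC, and qualify the conclusion if the two intervals disagree.

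**Cost:** one field in existing records and a short addition to the analysis text. The sample size need not change. The downside is a wider supplementary interval and an ICC that will be imprecise if nurses are few.

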### Allocation to trial arm

When a patient is identified as eligible for the study, and has given written, informed consent to take part, the researcher randomises the patient using a web-based programme hosted by the Primary Care Clinical Trials Unit (PC-CTU), University of Birmingham. Centre specific randomisation lists were produced by a statistician at the trials unit. Participants are individually randomised, stratified by centre. The four recruitment centres are Birmingham and West-Midlands South; Greater Manchester; North West Midlands and Oxfordshire/Gloucestershire. Only the PC-CTU have access to the allocation sequence.

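### The stated ANCOVA leaves out centre, the stratification factor, and allows a transformation that could move the primary SGRQ effect off the 4-point scale (minor)

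*Protocol article*

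**What the plan says.** Under Allocation to trial arm, the Protocol article states: "Participants are individually randomised, stratified by centre". It then lists the strata: "The four recruitment centres are Birmingham and West-Midlands South; Greater Manchester; North West Midlands and Oxfordshire/Gloucestershire". A trials-unit statistician prepared a separate list for each centre; the section does not mention blocking.

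Under Analysis, the method for continuous outcomes is: "For outcomes measured on a continuous scale (HRQoL, physical activity, EuroQol EQ-5D), analysis of covariance will be used". The article spells this out as "a linear regression where the final score is regressed against treatment group and adjusted for baseline score". Baseline score is the only covariate named, and centre appears in no model in that section. The next sentence reads: "Model assumptions will be checked and a transformation for Normality used if necessary". It gives no criterion, names no transformation, and does not exempt the primary outcome.

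Under Statistical justification for sample size, the target is set in raw SGRQ points: "To have 80% power to detect a difference of 4 points", a difference described as the one "which is the minimal clinically significant difference [26] from a baseline total value of 39".

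**The concern.** There are two separate issues in the same short piece of text.

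- **Centre.** A trial should normally be analysed by the factors it is randomised by. If allocation is balanced within centre, between-centre differences cannot contribute to the difference between arms. A model without centre still counts them as residual noise, so the standard error is too large and the test falls a little below its nominal level. Precision is given away in a trial sized at only 80% power.
- **Scale.** Whether the primary outcome is transformed is left to a check on the trial data. A mean difference in SGRQ points can be set against the 4-point threshold; an effect on a transformed scale cannot, at least not directly. The scale of the headline result should be fixed in advance.

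**Working it through.** **Inputs from the article:** difference 4, SD 15, 5% level (taken as two-sided), 80% power, 445 evaluable, 20% loss, 556 recruited, 278 per group, four centres. **Assumed, because the article gives no figure:** the share *s* of residual variance explained by centre, taken as 0-10%.

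**1. The article's sample size.** n per arm = 2 × (1.96 + 0.84)² × 15² / 4² = 221, or 442 in total. The t-based calculation gives 221.7 per arm, about 444 in total. Allowing for loss, 445 / 0.8 = 556.25. The stated 445 and 556 reproduce, and 445 / 2 is about 222 evaluable per arm.

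**2. Leaving out centre when the lists enforce balance within centre.**
- Standard error reported without centre: SE₀ = 2 × 15 / √445 = 1.422.
- True standard error of the estimate: SE₁ = SE₀ × √(1 − s).
- True size without centre: 2 × [1 − Φ(1.96 / √(1 − s))].
- Power without centre: Φ((4 − 1.96 × SE₀) / SE₁).
- Power with centre: Φ(4 / SE₁ − 1.96).

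Example at s = 10%: SE₁ = 1.422 × 0.949 = 1.349. The size is 2 × [1 − Φ(2.066)] = 3.9%. Power without centre is Φ(0.899) = 81.6%, and with centre Φ(1.005) = 84.3%.

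| Assumed centre share | True size without centre | Power without centre | Power with centre |
|---|---|---|---|
| 0% | 5.0% | 80.3% | 80.3% |
| 1% | 4.9% | 80.4% | 80.7% |
| 2% | 4.8% | 80.6% | 81.1% |
| 5% | 4.4% | 80.9% | 82.3% |
| 10% | 3.9% | 81.6% | 84.3% |

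The loss is therefore nil to about 2.7 percentage points. The table gives no credit for baseline adjustment. With an assumed baseline to 12-month correlation of 0.5, power at s = 10% is 91.3% without centre and 92.8% with it, a gap of about 1.6 percentage points.

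**3. Simulation.** Four centres with effects −3, −1, 1 and 3, residual SD 12, balanced allocation within centre, baseline in both models, 4,000 replicates. The implied share is 5 / (5 + 144) = 3.4%. Size was 4.6% without centre and 5.1% with it; power was 92.9% and 93.2%.

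**4. If the lists do not enforce balance.** SE₀ is then the correct standard error of the centre-free estimate, so the size is 5% and power is 80.3%. The cost is a standard error wider by 1/√(1 − s): 1.0%, 2.6% and 5.4% at shares of 2%, 5% and 10%. Power with centre is essentially as in the last column of the table.

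**5. Scale, using a log purely as illustration (the article names no transformation).** A fall of 4 from 39 is a ratio of 35/39 = 0.897. The same ratio is a fall of 2.1 points at a score of 20, 4.0 at 39 and 6.2 at 60. One transformed effect does not correspond to one difference in points.

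**The case against.** The strongest case on the other side has four parts.

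- **The centre effect may be nil.** The centre share is assumed, and baseline SGRQ, already in the model, may absorb much of any difference between centres. This stands, and it is why the range starts at 0%.
- **Balance is assumed.** Blocking is not stated, so a test below its nominal level cannot be asserted outright. This also stands. A reader might combine the 3.9% size with a rise in power from 80.3% to 84.3%, but those figures belong to different designs. Where balance is enforced, the comparator at a 10% share is 81.6%.
- **The transformation is conditional and probably aimed elsewhere.** The clause covers several outcomes. Physical activity in controls is put at 55 minutes with SD 70, which must be skewed, whereas SGRQ at 39 with SD 15 lies 2.6 SDs above zero. The section also offers a mean difference as an example effect estimate. A reader might infer that the primary estimand will change after the data are seen, or that the result will be uninterpretable. The text supports neither: it describes a possibility, and residuals can be checked without looking at the treatment effect. But HRQoL is named among the outcomes covered and is not exempted, so the risk remains.
- **A condensed article leaves detail to the analysis plan.** This holds for the logistic and Poisson models, for which no covariates are given, and no point is made about them. It holds less well for the ANCOVA, which the article defines explicitly with one covariate. A plan not shown may add centre or fix the scale; the published text does neither.

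**Conclusion.** The point holds, at minor severity. The stated primary model does not match the stratified design. If the lists enforce balance and centre explains 0-10% of residual variance, the true size is 5.0% down to 3.9% and the power loss is 0 to about 2.7 percentage points. Without enforced balance the size is nominal and the standard error is at most about 5% wider than it need be over that range.

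A reader might infer that ignoring the stratification factor biases the effect or produces false positives. It does neither: the estimate is unbiased and any error in size is on the conservative side.

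On scale, the finding is a risk: if the clause were applied to the SGRQ, the primary effect could not be read directly against 4 points. With about 222 evaluable per arm, inference on a mean difference does not depend on Normal residuals, so leaving this option open for the primary outcome gains little.

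**What to change.** State the primary model as 12-month SGRQ total regressed on treatment, baseline SGRQ and centre (four-level fixed effect), on the original SGRQ scale. If non-Normality is a worry, prespecify a robust or bootstrap confidence interval for the mean difference as a sensitivity analysis. Restrict any transformation to skewed secondary outcomes such as minutes of activity.

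This changes analysis wording only. Centre uses three degrees of freedom, and the sample size stays at 445 evaluable and 556 recruited.
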